### Intervention

#### Intervention Description

Participants will be randomly assigned to one of 3 arms. Arm 1: Ketamine-hydrochloride infusions alone, Arm 2: CBT in combination with MM (CBT/MM), or Arm 3: Ketamine-hydrochloride infusions in combination with CBT/MM.

Ketamine-hydrochloride will be delivered intravenously for patients in Arm 1 and Arm 3. For this study, 1 mg/kg of ketamine intravenous will be dosed by total body weight and administered over 2 hours up to a maximum dose of 100 mg as per our local institutional protocol.

#### Arm 1: Ketamine-Hydrochloride Infusion Alone

Patients in Arm 1 receiving a ketamine-hydrochloride infusion alone will receive ketamine infusions on weeks 2, 7, and 12 of the study. After the study intervention, participants will have their vital signs and adverse events monitored for one hour. The anesthesia provider will be responsible for assessing the participant before discharge. Participants will not be allowed to drive after the intervention; therefore, measures will be taken to ensure the participant has an adequate plan of transportation (ie, a companion or suitable transportation).

For safety reasons, the anesthesia provider administering the medication will not be blinded. However, the study personnel designated to collect the outcome data will be unaware of the treatment assignment. Patients will not be blinded to their therapy for the purposes of this feasibility study.

#### Arm 2: CBT/MM Alone

Participants in Arm 2 receiving CBT/MM alone will receive weekly CBT/MM treatment in collaboration with NexJ Health Inc and supplemented by the designated psychotherapist trained for and experienced in previous studies [13]. About 16 hours of CBT/MM therapy will be delivered over 16 weeks. Participants will be assigned to a 3-hour CBT/MM workshop remotely, to be administered by the delegated psychotherapist. The CBT-MM programming will combine exposure to smartphone- and computer-accessible workbooks with phone-based mental health counseling (16 hours in 16 weeks) that coordinates with ongoing software interactions (eg, secure text messaging) [14,15].

The software for delivering the CBT/MM therapy is a standalone platform, called “Connected Wellness Platform,” developed by NexJ Health Inc. Connected Wellness Platform is a customized, secure (2-level log-in with 128-bit encryption) interface accessible through both a smartphone and a computer.

#### Arm 3: Ketamine-Hydrochloride Infusion in Combination With CBT/MM

Finally, participants in Arm 3 receiving ketamine infusion+CBT/MM will receive both the standard CBT/MM and ketamine-hydrochloride infusion protocols as described above. Participants in this arm will have psychotherapy delivered concurrently with their ketamine infusions on weeks 2, 7, and 12 in person by the delegated psychotherapist. Participants in Arm 3 will also receive 16 weeks of CBT/MM remotely.

#### Hypothesis

In line with the primary aim of this study, this pilot study will prove to be feasible for a large-scale clinical trial. We expect that we will be able to successfully meet our recruitment target (30 participants) within the 1-year time frame of the study and expect this study withdrawal rate to be less than 10% (3/30 patients). Feasibility of this study will be determined by the following set variables and cutoff percentages; recruitment success with the specific aim to recruit all necessary patients within the first year of the trial period, adequate consent rate (30/100, >30% of eligible patients consent to participate in the study), intervention adherence as define by the percentage of patients who complete all medication and psychotherapy visits (27/30, >90%), percentage of patients who withdraw from the study (ie, due to side effects; 6/30, <20%), percentage of patients with incomplete pain intensity and pain interference data at 1 month, (eg, withdrawal due to side effects, loss to follow up, or missing data; 3/30, <10%), and rate of adverse outcomes. We do not foresee any issues arising with the protocol of the study or the delivery of each arm.

While not powered to examine these effects, we hypothesize that patients allocated to the combination ketamine and CBT/MM arm of this study will have the greatest reduction in pain intensity and pain interference.

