## Methods

### Aim

The primary objective of this study is to enroll 30 participants with chronic neuropathic pain and assess the feasibility of conducting a 3-arm parallel group pilot RCT. The secondary aim of the study is to examine whether the combined effects of ketamine and CBT/MM (as delivered through the NexJ Health Inc platform by trained navigator-coaches) can reduce pain intensity and pain interference by week 20 of the study (ie, limited efficacy at week 20).

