### Withdrawal Criteria

A participant will be withdrawn if the participant presents with a severe adverse event or unknown allergic reaction during the first administration of ketamine-hydrochloride or if the participant wants to withdraw from the study for any reason. The participant will receive the necessary treatment to alleviate any untoward events and will be monitored by the study physician until judged appropriate for discharge. Participants will be followed up on the following day to ascertain more details on their condition. Data from a participant who has been withdrawn will be collected up to the day following their withdrawal to ensure that the participant has no more complications. If a participant withdraws from the study at any time, the reasons for withdrawal will be collected and documented as a feasibility study outcome.

Since this is a feasibility study without a specific sample size required to analyze any outcome, participants will not be replaced or added.

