### Outcome Measures

#### Primary Outcome

The primary outcome of this pilot trial is to determine the feasibility of a large-scale multicenter trial. Feasibility outcomes will include the following variables, with all thresholds listed in parentheses:

Recruitment success (with the specific aim of recruiting all necessary patients within the first year of the trial period).Adequate consent rate (>30% of eligible patients consent to participate in the study).Percentage of patients who complete all medication and psychotherapy visits (ie, intervention adherence; >90%).Percentage of patients who withdraw from the study (eg, due to side effects or other reasons; <20%).Percentage of patients with incomplete pain intensity and pain interference data at 1 month and stated or ascribed reason (eg, withdrawal due to side effects, loss of follow-up, or missing data; <10%).Rate of adverse outcomes (ie, 0 serious adverse events).

Based on the result for each primary feasibility outcome, we will determine whether the definitive study is feasible as proposed (ie, all feasibility targets are met), feasible with protocol modifications (modifications specified), or not feasible because feasibility targets could not be met even with protocol modifications. These cutoffs, identified in the parentheses above, will help determine whether protocol changes are required before proceeding with a definitive trial.

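### The withdrawal feasibility target counts side-effect withdrawals in one section and all withdrawals in another, at the same <20% cut-off

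*Protocol article*

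**What the plan says.** The Hypothesis section of the Protocol article introduces its list of criteria as decisive: "Feasibility of this study will be determined by the following set variables and cutoff percentages". The withdrawal item in that list reads "percentage of patients who withdraw from the study (ie, due to side effects; 6/30, <20"%).

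The Primary Outcome section lists the same criterion as "Percentage of patients who withdraw from the study (eg, due to side effects or other reasons; <20"%). It then requires every target to be met before the definitive trial is called "feasible as proposed (ie, all feasibility targets are met").

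Withdrawal Criteria includes the case "or if the participant wants to withdraw from the study for any reason" and adds that "the reasons for withdrawal will be collected and documented as a feasibility study outcome". The Aim section sets the denominator: "enroll 30 participants with chronic neuropathic pain". Withdrawal Criteria rules out replacements, so it stays at 30.

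The Hypothesis section also states an expectation, separate from the cut-off, that withdrawal will be below 10% (3/30).

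**The concern.** *Ie* restricts and *eg* illustrates, and the Primary Outcome wording also names reasons other than side effects. Read literally, the two sections apply one cut-off to two different counts. Nothing in the article says which count governs.

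At stake is the result for one of the six primary feasibility targets. The same set of records could be reported as meeting it or missing it, and the choice could be made after the data are seen. The Primary Outcome section uses the cut-offs to decide whether the protocol must change before a definitive trial, so the choice also bears on whether attrition is flagged as something to modify. The narrow count fits Arm 2 poorly, since those participants receive no ketamine. In every arm it leaves out people who stop for other reasons.

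**Working it through.** **Inputs.** n = 30 (Aim), no replacement (Withdrawal Criteria), cut-off <20% (Hypothesis and Primary Outcome), adherence target >90% and incomplete-data target <10% (both sections), treatment and follow-up weeks (Table 1).

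**1. The plan's own figure.** 6/30 = 0.200, so the count and the percentage agree as arithmetic. The rule is strict, however, so 6/30 itself fails. The largest passing count is 5 (5/30 = 16.7%).

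**2. Where the definitions disagree.** Let t be total withdrawals and s those due to side effects, with s ≤ t.

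- Narrow count passes: s/30 < 0.20, that is s ≤ 5.
- Broad count passes: t/30 < 0.20, that is t ≤ 5.
- They disagree exactly when t ≥ 6 and s ≤ 5. Because s ≤ t, the narrow count can pass while the broad one fails, but never the reverse.

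Examples:

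- t = 6, s = 2 gives 2/30 = 6.7% (met) against 6/30 = 20.0% (missed).
- t = 8, s = 4 gives 4/30 = 13.3% (met) against 8/30 = 26.7% (missed).

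**3. Does the overall verdict change?** Adherence means completing all medication and psychotherapy visits, >90%. Since 27/30 = 90.0% fails and 28/30 = 93.3% passes, at most 2 participants may be non-completers.

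- Six withdrawals during treatment leave at most 24/30 = 80%; eight leave at most 22/30 = 73.3%. Adherence is then missed under either withdrawal count.
- For adherence to survive with t = 6, at least 6 − 2 = 4 must withdraw after their last treatment visit. With t = 8 it is at least 6. By Table 1 that window runs from after week 12 (Arm 1) or after week 16 (Arms 2 and 3) to week 20. No more than 2 participants in total could miss any treatment visit.
- The incomplete-data target allows at most 2 of 30, since 3/30 = 10.0% fails. The article does not say from when its 1 month runs. If it falls at week 20, withdrawals in that late window would miss this target too.

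**4. How likely is disagreement on the single target?** The chance of meeting it is P(X ≤ 5) = Σ(k=0 to 5) C(30,k) p^k (1−p)^(30−k), with p the side-effect rate for the narrow count and the all-cause rate for the broad one. The gap is the probability of disagreement. The rates are assumptions; the documents give only the expectation of under 10%.

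| All-cause rate | Side-effect rate | Narrow count met | Broad count met | Gap (points) |
|---|---|---|---|---|
| 10% | 5% | 99.7% | 92.7% | 7.0 |
| 15% | 5% | 99.7% | 71.1% | 28.6 |
| 20% | 10% | 92.7% | 42.8% | 49.9 |
| 25% | 12.5% | 83.6% | 20.3% | 63.3 |

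**The case against.** The best reply is that this is a slip of *ie* for *eg*. The Primary Outcome section is where the thresholds are formally set, and it counts all reasons. Withdrawal Criteria does the same. The noun phrase in the Hypothesis item is itself unrestricted, and the next item in that list uses *eg* for a parallel set of examples. This is probably right, and it shows which way to correct. It does not remove the conflict, because the Hypothesis section says its own list determines feasibility.

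A second reply concerns consequence. A reader might infer that this one phrase can turn the pilot's overall conclusion. The documents do not support that except in a narrow case: disagreement needs at least 6 withdrawals, and unless nearly all of them follow the last treatment visit, the adherence target has already failed. Missing a target also does not by itself mean the trial is not feasible, since both the Primary Outcome and Outcome Analysis sections allow a verdict of feasible with modifications. This reply stands.

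A third reply is that attrition for planning is not lost. Reasons are recorded for every withdrawal, so the all-cause figure can be computed whichever count is tested against the cut-off. This also stands; only the pass or fail result is affected.

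**Conclusion.** The inconsistency is real, sits in current text and affects a primary decision criterion. Its effect is confined to the result for the withdrawal target and the modifications that result would prompt. It reaches the overall verdict only if, with 6 withdrawals, at least 4 come after the participant's last treatment visit, and even then only if no other target fails.

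At a 10% all-cause rate split evenly by cause, the probability of a discordant result is about 7 percentage points. Gaps such as 83.6% against 20.3% need an assumed 25% withdrawal rate, at least 2.5 times the protocol's own expectation, and should not be taken as the likely size. All these probabilities assume independent withdrawals at a common rate and a fixed denominator of 30. The region of disagreement (t ≥ 6, s ≤ 5) needs no assumed rates.

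**What to change.** In the Hypothesis section, replace the parenthetical restriction to side effects with withdrawal for any reason, so that it agrees with Primary Outcome and Withdrawal Criteria. Apply <20% to all-cause withdrawal and state the largest passing count, 5 of 30, in place of 6/30. Report side-effect withdrawals on a separate descriptive line, using the reasons already being collected.

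The cost is one phrase and one count; no new data or participants are needed. The article reports that recruitment had not begun as of November 1, 2023. If the change is made before data accrue, it also removes a choice that could otherwise be made after the fact. The downside is that the target is somewhat harder to meet than under the side-effect-only wording.

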#### Blinding Mechanism

The intervention delivery providers (anesthesiologists and psychologists) and other members of the research team will be aware of each participant’s assigned intervention. Within the research team, blinded members will be responsible for inputting all of the data into the REDCap (Research Electronic Data Capture; Vanderbilt University) database, with the exception of any ketamine-specific data, that is, semistructured interviews after the ketamine intervention and any adverse events. Following data collection, we will request blinded staff to record their “best guess” of each patient’s intervention to assess blinding efficacy. The research team currently has 1 blinded member who will serve as the outcome assessor and be responsible for data input.

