### Recruitment and Randomization

Recruitment will occur at the Chronic Pain Clinic at St. Michael’s Hospital, Toronto, Ontario. The clinic receives approximately 1000 referrals per year. An estimated 3% of these referrals would be eligible for inclusion in this trial.

A staff member who does not belong to the study team will be provided with the instructions to use a remote random number generator, the “Sealed Envelope” website to generate an allocation sequence at random. The allocation list will be sent to the Research Pharmacy staff at St. Michael’s Hospital directly, without the knowledge of the study team, to maintain the blindness. After participant enrollment, the pharmacy staff will randomize the patient and inform a delegated research team member as to the allocated intervention arm. The delegated unblinded research team member will then notify the patient which arm they have been randomized to and will coordinate with the anesthesiologists and psychologists, who will be unblinded, to schedule in-person study visits on weeks 2, 7, and 12 according to the randomized treatment arm. For patients randomized to Arm 1 or 3, the Research Pharmacy staff will prepare ketamine-hydrochloride for weeks 2, 7, and 12. The outcome assessors are the only research staff to remain blinded to patient treatment (currently, we only have 1 delegated outcome assessor).

Participants will be randomized to receive either (1) ketamine-hydrochloride infusions alone, (2) CBT/MM alone, or (3) a combination ketamine-hydrochloride infusion and CBT/MM.

Participants will be eligible for this study as per the inclusion and exclusion criteria listed (Textbox 1).

Inclusion and exclusion criteria regarding participant eligibility for PYSKED-NP.

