**Assessments**								
	Baseline data		✓					
	Semistructured interviews		✓^c,d^	✓^d^	✓^d^	✓^d^		✓^c,d^
	Pregnancy test (if applicable)^e^			✓	✓	✓		
	Questionnaires: PROMIS-PI^f^, PGIC^g^, GAD-7^h^, PHQ-9^i^, and PCS^j^		✓	✓	✓	✓	✓	✓
	Adverse events			✓	✓	✓	✓	✓

^a^MINI: Mini International Neuropsychiatric Interview.

^b^CBT/MM: cognitive behavior therapy/mindfulness and meditation.

^c^Participants randomized to receive CBT/MM alone (arm 2), will receive a semistructured interview on weeks 1 and 20.

^d^Participants randomized to receive ketamine-hydrochloride infusion + CBT/MM (arm 3) will receive a semistructured interview on weeks 1 and 20 as well as a semistructured interview during the ketamine infusion on weeks 2, 7, and 12.

^e^Only female participants randomized to receive ketamine-hydrochloride alone (arm 1) or the ketamine-hydrochloride infusion + CBT/MM (arm 3) will require a pregnancy test on the day of infusion.

^f^PROMIS-PI: Patient-Reported Outcomes Measurement Information System.

^g^PGIC: Patient Global Impression of Change Scale.

^h^GAD-7: Generalized Anxiety Disorder-7.

^i^PHQ-9: Patient Health Questionnaire-9.

^j^PCS: Pain Catastrophizing Scale.

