## Discussion

It is hypothesized that concurrent pharmacotherapy and psychotherapy have combined effects on the analgesic response. In addition to ketamine’s anesthetic-analgesic properties, it also uniquely alters the individual’s level of consciousness at variable doses. Some researchers posit that the therapeutic experience of psychotherapy may be augmented by ketamine’s alteration of conscious awareness [10]. As demonstrated by this systematic review, few studies have examined ketamine-assisted psychotherapy (KAP) for chronic neuropathic pain. RCTs have not been published on this topic. In addition, there appears to be wide variability in the indication, dosage, and patient treatment setting, such that the current literature is inconclusive.

The 3-arm design allows us to compare the feasibility of KAP with ketamine alone and CBT/MM. We will track feasibility outcomes, including recruitment rate and adverse event rate, to estimate the acceptability of this intervention compared to controls. There are also limitations to this study. Due to the participatory nature of CBT/MM, we are unable to blind patients and the research team to patients’ assigned interventions. To mitigate this, the outcome assessors will be blinded to minimize bias, and we will request and report their “best guess” estimate of each patient’s assigned intervention at the end of the study. We also recognize that there may be different patient outcomes based on the mode of CBT/MM delivery. Patients in arm 1 receiving ketamine alone will have no CBT/MM as part of the trial design. Patients assigned to CBT/MM alone (Arm 2) will be receiving their intervention sessions remotely rather than in-person for 16 weeks. Patients in Arm 3 will be receiving ketamine on weeks 2, 7, and 12 and in-person CBT/MM at this time. They will also be involved with remote CBT/MM sessions from weeks 1 to 16 (except for weeks 2,7, and 12). This hybrid intervention will allow us to collect data on the feasibility of in-person versus remote psychotherapy for this patient population.

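### The one blinded assessor also enters the trial data, and the data-entry exception covers ketamine records but not CBT/MM records, so Arm 1 can be told apart from Arms 2 and 3

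*Protocol article*

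**What the plan says.** **Who enters data.** Under Blinding Mechanism, "blinded members will be responsible for inputting all of the data into the REDCap" database, "with the exception of any ketamine-specific data, that is, semistructured interviews after the ketamine intervention and any adverse events". The same section adds: "The research team currently has 1 blinded member who will serve as the outcome assessor and be responsible for data input".

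**What blinding is claimed.** Recruitment and Randomization states: "The outcome assessors are the only research staff to remain blinded to patient treatment". The Arm 1 section says that those who collect outcome data will not know the assignment. Follow-Up Data schedules telephone follow-up to protect blinding. The Discussion concedes that patients and the wider team cannot be blinded and answers: "To mitigate this, the outcome assessors will be blinded to minimize bias".

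**What treatment-specific data exist.** One primary feasibility outcome is the "Percentage of patients who complete all medication and psychotherapy visits", with a threshold above 90%. Outcome Analysis says that missed sessions will be documented. The Discussion says that Arm 1 has no CBT/MM. Footnote c of Table 1 reads: "Participants randomized to receive CBT/MM alone (arm 2), will receive a semistructured interview on weeks 1 and 20". Footnote d gives Arm 3 interviews at the same two weeks plus the infusion weeks. Neither footnote gives Arm 1 an interview.

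**The blinding check.** After data collection, blinded staff record a best guess of each patient's arm.

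**The concern.** The exception shows that the authors recognised that treatment records can reveal the arm, but it covers only the ketamine side. Records that exist only for patients receiving CBT/MM are just as informative about Arm 1, and the rule leaves them with the one person who is meant to stay blinded. No second blinded assessor is available if that person learns the arm.

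The safeguard at stake is the one that the Discussion offers against bias in an open-label comparison. An assessor who knows the arm could prompt or clarify differently when giving questionnaires in person or by telephone. The best-guess check would also be harder to interpret. A high rate of correct guesses could come from the data-entry duty alone, and planners of the definitive trial might wrongly conclude that assessor blinding cannot be achieved.

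**Working it through.** The article gives no figure for blinding success, so there is nothing to reproduce. The check has two parts.

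**1. Which records fall inside the exception?**

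| Record | Arms that have it | Covered by the exception? |
|---|---|---|
| Interviews after ketamine | Not Arm 2 | Yes, named |
| Adverse events | All | Yes, named |
| CBT/MM visit completion | 2 and 3 | No |
| Week 1 and week 20 interviews | 2 and 3 by the Table 1 footnotes; Secondary Outcome names no arm | No, but entry in REDCap is not stated |
| Infusion visits, pregnancy tests | 1 and 3 | Unclear: ketamine-specific in ordinary language, but not in the list that defines the term |
| In-person or remote CBT/MM session | Discussion: Arm 2 remote only, Arm 3 partly in person. Table 1: in person for both | Not covered, and the two places conflict |

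The CBT/MM completion row is enough for the point. The exception does not reach it, it is needed for a primary feasibility outcome, and Arm 1 cannot have such a record.

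**2. How much does this reveal?**

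Inputs: 30 participants (Aim) and three arms. The allocation ratio is not stated, so 10 per arm is assumed.

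- *Blinding intact.* A random guess among three arms is right with probability 1/3, so the expected number right is 30 × 1/3 = 10 (33%).
- *Assessor sees only whether CBT/MM records exist.* Arm 1 is certain, and Arms 2 and 3 are a 1-in-2 guess. The expected number right is 10 × 1 + 20 × 1/2 = 20 (67%).
- *Could 20 or more arise by chance?* With independent guesses, P(X ≥ 20), where X ~ Binomial(30, 1/3), is 0.00019, or about 0.0002. The check would therefore show a clear failure.
- *Sensitivity to the allocation assumption.* If Arm 1 has n₁ patients, the expected number right is n₁ + (30 − n₁)/2 = 15 + n₁/2. For n₁ = 8 this is 19, and for n₁ = 12 it is 21. The random-guess figure stays at 10.

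The step from 20 to 30 right needs a record that separates Arm 2 from Arm 3. Session mode would do so under the Discussion's account, but not under Table 1's.

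**The case against.** **Nobody says that the assessor enters attendance.** The article does not name who records CBT/MM sessions. These run through a separate platform, and an unblinded delegate already coordinates the in-person visits. This stands as a limit: the duty is inferred from the instruction that blinded staff input all data. But that is its plain meaning, and the stated exception does not remove it.

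**The interviews may never reach REDCap.** Secondary Outcome describes audio recording, restricted storage and transcription by the research team, without mentioning REDCap, and it names no arm. This stands too, so the interview route is conditional. The point does not depend on it.

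**This is operational detail that an article leaves out.** That would be a good answer to silence. Here the article states a rule, defines its exception and assigns both duties to one person. The defect lies in the stated rule.

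**The bias at stake is small.** Patients know their arm and answer the questionnaires themselves, the clinical outcomes are secondary in a pilot that is not powered for them, and the best-guess check would expose a breach. Most of this stands and limits the importance of the point. The check would, however, detect the problem without preventing it.

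**A stronger reading.** A reader might infer that the assessor can identify all 30 patients, using pregnancy tests or infusion visits to separate Arm 2 from Arm 3. The documents do not support this. Those records can reasonably be read as ketamine-specific and so withheld, and pregnancy tests apply only to some female participants. Session mode does not settle it either, because Table 1 and the Discussion disagree on whether Arm 2 has in-person sessions.

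**Conclusion.** The point holds in a limited form. Followed as written, the data-entry rule gives the sole blinded assessor records that separate Arm 1 from Arms 2 and 3. Expected correct guesses rise from about 10 of 30 to about 20 of 30.

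This rests on two assumptions: roughly equal allocation, and CBT/MM completion being entered under the general rule. It does not show that blinding fails completely, or that every arm is known from week 1. Week 1 records would at most set Arm 1 apart from the other two.

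The rule weakens a safeguard that the article invokes in several places. Any resulting bias in patient-reported secondary outcomes is likely to be modest. The correction is worth making because it is cheap and recruitment had not begun on the article's status date of November 1, 2023.

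**What to change.** Under Blinding Mechanism, widen the exception from ketamine-specific to all treatment-specific data:

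- Name CBT/MM attendance and all semistructured interviews, and state explicitly that infusion visits and pregnancy tests are included alongside adverse events.
- Have the existing unblinded team member enter these in REDCap forms that the assessor cannot open.
- Limit the blinded assessor to the outcome questionnaires: the pain Numeric Rating Scale, PROMIS-PI, PCS, PHQ-9, GAD-7 and PGIC.
- Record the best guess immediately after each participant's week 20 assessment.

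Separately, reconcile Table 1 with the Discussion on whether Arm 2 has in-person CBT/MM.

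The cost is a change of wording, REDCap access rights, and a small shift of data entry to the unblinded member. Someone other than the assessor must already enter the excepted ketamine data, so no new role is needed.
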